## Abstract

**Background: **WHO’s 2015 End TB Strategy advocates social and economic (socioeconomic) support for TB-affected households to improve TB control. However, evidence concerning socioeconomic support for TB-affected households remains limited, especially in low-income countries.

**Protocol: **This mixed-methods study in Nepal will: evaluate the socioeconomic impact of accessing TB diagnosis and care (Project 1); and create a shortlist of feasible, locally-appropriate interventions to mitigate this impact (Project 2). The study will be conducted in the Chitwan, Mahottari, Makawanpur, and Dhanusha districts of Nepal, which have frequent TB and poverty.

The study population will include: approximately 200 people with TB (Cases) starting TB treatment with Nepal’s National TB Program and 100 randomly-selected people without TB (Controls) in the same sites (Project 1); and approximately 40 key in-country stakeholders from Nepal including people with TB, community leaders, and TB healthcare professionals (Project 2).

During Project 1, visits will be made to people with TB’s households during months 3 and 6 of TB treatment, and a single visit made to Control households. During visits, participants will be asked about: TB-related costs (if receiving treatment), food insecurity, stigma; TB-related knowledge; household poverty level; social capital; and quality of life.

During Project 2, stakeholders will be invited to participate in: a survey and focus group discussion (FGD) to characterise socioeconomic impact, barriers and facilitators to accessing and engaging with TB care in Nepal; and a one-day workshop to review FGD findings and suggest interventions to mitigate the barriers identified.

**Ethics and dissemination: **The study has received ethical approval. Results will be disseminated through scientific meetings, open access publications, and a national workshop in Nepal.

**Conclusions: **This research will strengthen understanding of the socioeconomic impact of TB in Nepal and generate a shortlist of feasible and locally-appropriate socioeconomic interventions for TB-affected households for trial evaluation.

## Introduction

Tuberculosis (TB) disease, which kills 1.5 million people annually, is driven by poverty
^1^. Having TB disease can also worsen impoverishment through loss of income and costs of accessing care
^2–
5^. Such costs can become “catastrophic”, leading patients to abandon treatment, develop drug-resistance, and die
^6^. WHO’s 2015 End TB Strategy advocates elimination of catastrophic costs and provision of socioeconomic support for TB-affected households
^5^. Nevertheless, there is minimal evidence concerning the ideal interventions to realise this policy change
^6–
10^. This research will generate preliminary evidence to fill this knowledge gap in a low-income country: Nepal. The findings will inform a randomised controlled trial of socioeconomic support for TB-affected households in Nepal.

Research from Peru has demonstrated that the severe socioeconomic impact of TB can lead to catastrophic costs (defined by WHO as >20% of a household’s annual income)
^6^. The same team also demonstrated that socioeconomic interventions for TB-affected households can mitigate catastrophic costs (
Figure 1a), improve TB preventive therapy uptake (
Figure 1b), and increase TB treatment success (
Figure 1c)
^11–
15^.

**Figure 1. f1:**
[figure not shown]
**a**) Catastrophic costs incurred by intervention (n=135) and control (n=147) TB-affected households of Callao, Peru.
**b**) Preventive therapy initiation in household contacts of intervention (n=206) and control (n=204) TB-affected households of Callao, Peru.
**c**) TB treatment success in patients from intervention (n=135) and control (n=147) TB-affected households of Callao, Peru. Part
**a**) has been reproduced with permission from Wingfield
*et al.*
^13^ Parts
**b**) and
**c**) have been reproduced with permission from Wingfield
*et al.*
^15^.

However, despite these encouraging findings, Peru is a middle-income country with a strong TB program and existing national cash-transfer schemes. To make this research replicable and applicable in diverse settings, interventions similar to those in Peru need to be adapted to other country contexts, especially low-income countries (LICs) with less developed social protection schemes and high TB burden. One such country is Nepal.

The estimated incidence of TB in Nepal is 154/100,000 people with 45,000 cases of TB being notified. Amongst these cases, there were 6,800 TB-related deaths. Multi-drug resistance (MDR) rates were 2.2% in new cases and 15% among retreatment cases. Importantly, despite good treatment success rates overall of more than 90% reported in Nepal, there remain shortcomings in TB care: treatment success rates were 70% for patients with MDR-TB and only 9% for those with HIV-TB co-infection; and accessibility of TB care remains low with treatment coverage of 70%
^16^.

The poor treatment coverage in Nepal may, in part, be due to the financial impact on TB-affected households, which is estimated to be high
^17^. Responding to this estimated burden, the Nepal National TB Programme (NTP) national strategic plan for 2016–2021 identifies provision of a support package to TB-affected households (specifically targeting MDR-TB-affected households) as a priority aim for the country with the goal of reducing catastrophic costs. There is currently limited evidence concerning the potential acceptability, impact, or cost-effectiveness of such a package, with which to inform and guide this policy decision. A cohort study has suggested that, during their illness, TB patients in Nepal experience decreased income and the total costs of accessing free TB treatment equate to nearly one quarter of annual household income
^17^. Further studies in Nepal have shown that clinic fees make up the largest proportion of direct costs and that TB patients who are poorer, are migrants, or are from rural areas, experience a disproportionate burden of total costs
^18–
20^. It is vital that vulnerable TB patient households most at risk of incurring TB-related costs are identified in order to prevent and cure TB and mitigate further impoverishment and its consequences. In non-randomized studies, incurring higher TB-related costs and not receiving education about TB have both been found to be associated with worse TB treatment adherence and adverse TB treatment outcomes
^18,
21^. Therefore, the financial impact of having TB disease in Nepal constitutes a challenge to achieving TB control and elimination.

To date, no study of TB-affected households’ costs in Nepal has been performed using the standardised global methodology for measuring costs related to accessing and engaging with TB care: the WHO TB Patient Costs Survey
^22,
23^. The studies above collected data at only one time point rather than repeated time points (e.g. cross-sectional rather than longitudinal) and did not robustly analyse the socioeconomic position, nutritional status, coping strategies, or linkage to social protection of TB-affected households. There have been no trials of socioeconomic support for TB-affected households in Nepal but formative qualitative analysis and a non-randomized pilot interventional study (offering education and financial support to patients with MDR-TB) suggested improved treatment outcomes
^24^.

However, studies reporting quantitative data alone will be insufficient to influence and change policy. Interaction with and among stakeholders has been described as the key facilitator for knowledge translation and evidence-informed health policymaking
^25^. These interactions can include policy dialogues between stakeholders to deliberate on a priority topic. Therefore, complementary to quantitative data, the focus group discussions (FGDs) and workshop detailed within this protocol will aim to expand a policy dialogue on socioeconomic support for TB-affected households among key stakeholders in Nepal, from people with TB to community leaders to TB healthcare professionals. Policy dialogues represent knowledge translation to support the integration of research evidence with tacit knowledge of local health policy-makers to: inform future policy decisions in often complex and dynamic contexts; and foster proactive collaboration
^26,
27^. These elements will be critical for successful implementation of any future interventions
^28^.

In summary, this mixed-methods research will complement and extend the existing knowledge base on social determinants and consequences of TB. More specifically, the culmination of the research will be the creation of a shortlist of feasible and locally-appropriate socioeconomic interventions for TB-affected households for future randomized controlled trial evaluation in Nepal.

## Protocol

### Ethical statement

Ethical approval was granted from the University of Liverpool, UK, research ethics committee in April 2018 (approval number 2436) and then the National Health Research Council of Nepal (NHRC) research ethics committee in May 2018 (approval number 320/2018).

Participant information leaflets will be provided and written informed consents will be obtained from all study participants for Project 1 Interviews (separate consent forms and information leaflets for patients and healthy controls), Project 2 Surveys, FGDs, and the workshop. These documents are available in the Extended Data section attachments
^29^.

All medical records obtained from the Nepal NTP will be kept confidential. Practically, through liaison with NTP Project Staff (as already organised for IMPACT-TB), the PM, PI, and RA will photocopy patient records from the Nepal NTP TB register obscuring the patient’s identifiable details. Photocopies will be marked with that patient’s unique study number identifier. No individual patients will be identifiable from publications resulting from this study.

### Study design

This mixed-methods study was funded by a Wellcome Trust Seed Award in Science (awards provided to early-career researchers to develop a novel idea that will go on to form part of a larger grant application) and will be divided into two complementary projects. Project 1 consists of a cohort study characterising the socioeconomic impact of TB on TB-affected households and a nested case-control study examining the social determinants of TB. Project 2 consists of a mixed quantitative-qualitative cross-sectional study using surveys, FGDs and a workshop to identify the barriers and facilitators to accessing and engaging with TB diagnosis and care in Nepal and suggesting potential interventions to mitigate the socioeconomic impact and improve access and engagement. The study will take place within the infrastructure of the larger EU-Horizon 2020 funded “IMPACT-TB” project, which is a study evaluating proven TB active case-finding (ACF) interventions in Nepal and Vietnam (grant 733174,
http://www.impacttbproject.org/).

### Primary aims

The primary aim of Project 1 is to evaluate the socioeconomic impact on TB-affected households of accessing and engaging with TB diagnosis and care in Nepal and compare that impact in people with TB identified through standard passive case finding (PCF) versus ACF. The primary aim of Project 2 is to collaborate with key stakeholders in Nepal to create a shortlist of potentially feasible and locally-appropriate socioeconomic interventions to mitigate this impact.

### Secondary aims

The secondary aim of Project 1 is to compare the social determinants of TB (including socioeconomic position, housing situation, knowledge about TB, comorbidities, quality of life, food security, and social capital) in people with TB versus people without TB from the same districts. The secondary aim of Project 2 is to collate the opinions of key stakeholders from diverse sectors about barriers and facilitators to accessing and engaging with TB care in Nepal.

An additional aim across the study is to generate a policy dialogue and form a collaborative research network to support development and implementation of a future randomised control trial of socioeconomic support for TB-affected households in Nepal.

### Study setting

The study will take place within the infrastructure of the larger IMPACT-TB study, which works with a well-established international non-governmental organisation, Birat Nepal Medical Trust (BNMT), to implement ACF activities including sputum-microscopy camps and roll-out of GeneXpert OMNI in four intervention and two control districts (with PCF only). The four districts are located in the central development region of Nepal and were selected for the IMPACT-TB project based on comparable populations and TB case detection rates (
Figure 2).

**Figure 2. f2:**
[figure not shown]
Map, population, and TB case notification rate of the four study site districts. Data for population and TB cases notification rate shown is taken from the Nepal TB Centre 2018 report. The four study site districts are labelled and highlighted in blue and green.

The primary outcome of IMPACT-TB is the effect of ACF on early TB case detection and the study does not involve support packages for TB-affected households during treatment. This presents a unique opportunity for the complementary research described in this protocol to add value to IMPACT-TB, explore the socioeconomic impact of accessing TB care, and shortlist locally-driven strategies to reduce this impact.

### Study population

***Participant identification, recruitment and follow-up***. During Project 1, approximately 200 people with TB (cases) consecutively recruited to Work Package 3 (WP3) of IMPACT-TB (Health Economic Analysis) in the four study sites will be further recruited to this study. 100 of these cases will have been diagnosed through ACF and 100 diagnosed through PCF. Whilst attending the NTP TB clinic, these people with TB will be invited to participate in this mixed-methods research with a separate written, informed consent (see Project 1 Interview Patient Consent Form,
*Extended data*)
^29^. During months three and six of their TB treatment, household visits will be conducted by BNMT project staff including community mobilisers.

Concurrently, 100 people without TB from the study sites (controls) will be invited to participate with written, informed consent (see Project 1 Interview Healthy Control Consent Form,
*Extended data*)
^29^. Due to constraints in study budget, duration, and field logistics, it will not be possible to age and sex match cases and controls nor to randomly select controls using geospatial or other household randomisation techniques. Therefore, a convenience sampling strategy was used. In order to be as widely representative of and generalisable to the background population as possible, following project team and community mobiliser discussions in the study sites, we opted to recruit control participants from diverse locations within the districts, which were attended by a broad demographic cross-section of the local population in terms of age, gender, and socioeconomic position. These diverse study site locations include: tea houses, primary healthcare centres, antenatal and immunization clinics, door-to-door visits following sputum camps (e.g. people who tested negative for TB), and public gathering places. Interviewers will visit the control recruitment locations at similar times of the morning and aim to consecutively recruit all individuals in attendance at that location. Similar numbers of participants from each recruitment location will be recruited until the sample size of 100 people without TB is reached. We acknowledge that convenience sampling may be associated with a higher likelihood of a non-generalisable control cohort than other techniques. To try to address this, the survey used to collect data from the controls has incorporated multiple questions concerning sociodemographic variables, including education level, occupation, amenities, and assets, from the most recent version of the Nepal Household Survey, which is publicly available. Descriptive analysis will evaluate whether the controls recruited are representative of the wider population in those districts through comparison of their sociodemographic data with respondents to the national survey in the same districts. Any differences between the control population and background population will then be highlighted transparently in corresponding research outputs and publications.

Project 1 inclusion criteria for Cases included: being a person with TB notified to the NTP and recruited to WP3 of the IMPACT-TB study; being aged 18 years or above; and giving verbal and written informed consent to participate. Project 1 exclusion criteria for Cases included: being under 18 years of age; being a person with TB not notified to the NTP and/or not recruited to WP3 of the IMPACT-TB study; being a person with TB notified to the NTP but with a recorded domiciliary address outside of the study site districts; and being unable or unwilling to give written and/or verbal informed consent to participate.

Project 1 inclusion criteria for Controls included: being 18 years or above with primary residence in the study site communities; not currently known to be a person with TB or have a member of the household currently known to be a person with TB (e.g. not diagnosed or notified or receiving TB treatment); and giving verbal and written informed consent to participate. Project 1 exclusion criteria for Controls included: being under 18 years of age; not having primary residence in the study site communities; known to be a person with TB or have a household member with TB currently (e.g. diagnosed and/or notified and/or receiving TB treatment); and being unable or unwilling to give verbal and written informed consent to participate. 

To generate the population for Project 2, a literature review and desk-based scoping review will identify a list of key in-country stakeholders from Nepal from diverse groups including: civil-society representatives; community leaders; and TB healthcare professionals including NTP managers and multi-disciplinary staff. Approximately 50 stakeholders will be selected through purposive sampling and invited to participate in: a pre-FGD survey, FGD, and a one-day workshop. A subset of purposively sampled TB patients recruited to Project 1 (including those with multi-drug resistant TB) will be among the stakeholders invited to participate.

Project 2 inclusion criteria include: being aged 18 years or above; belonging to a stakeholder group as defined above and/or identified during scoping exercise; and being able and willing to provide verbal and written, informed consent. Exclusion criteria for Project 2 are not meeting the inclusion criteria and/or being a person with TB who has not yet taken two weeks of TB treatment or is otherwise considered to still be infectious (e.g. MDR-TB with positive sputum smear or culture).

***Sample size and statistical power***. The sample size for Project 1 is approximately 200 Cases recruited to WP3 of the IMPACT-TB project and 100 Controls from the four study site districts. This sample size is opportunistic and pragmatic: related research suggests that data from 100 people with TB gives a representative spread of costs for a given context
^30,
31^.

For Project 2, each FGD will consist of approximately eight stakeholders. The estimated number of FGDs at which information power (or saturation level) will be reached is six
^12^. Thus, the sample size for Project 2 is approximately 40 stakeholder participants. We will invite 55 stakeholders as a contingency because we anticipate an attrition rate of 20–30% during the course of Project 2.

Given that this Seed Award research will be exploratory, preparatory (e.g. for the future trial), and does not include an intervention, no calculations of statistical power are required.

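### Part of the control group comes through health services or TB screening, routes linked to three of the compared variables; the net direction of the bias is uncertain and the planned check cannot detect it

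*Protocol article*

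**What the plan says.** Under Study population, the article says that "it will not be possible to age and sex match cases and controls nor to randomly select controls", and it adopts a convenience sample. Besides tea houses and public places, the locations listed are "primary healthcare centres, antenatal and immunization clinics, door-to-door visits following sputum camps (e.g. people who tested negative for TB"; the wording leaves open that there are others. At each place interviewers "aim to consecutively recruit all individuals in attendance at that location". Then: "Similar numbers of participants from each recruitment location will be recruited until the sample size of 100 people without TB is reached".

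The control criteria exclude known current TB in the person or the household. They set no condition on other illness, on the reason for being at the location, or on recent TB testing.

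Secondary aims lists what is compared between people with and without TB, including "knowledge about TB, comorbidities, quality of life, food security, and social capital".

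The article accepts that convenience sampling may give a control group that does not generalise. Its planned check is a "comparison of their sociodemographic data with respondents to the national survey in the same districts", using items such as education, occupation, amenities and assets.

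**The concern.** A control group should show how common a characteristic is in the population that gave rise to the cases. That fails when the route into the control group depends on the characteristic itself. Someone found at a primary healthcare centre may be more likely than a neighbour to have another illness or a poorer quality of life. Someone visited after a sputum camp has just had contact with TB services and may know more about TB. Someone at an antenatal or immunization clinic may be younger and healthier than the average adult.

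This is more specific than the general caveat in the article. The controls could match the national survey on every sociodemographic item and still differ from the population in illness, quality of life or TB knowledge. Adjusting for age, sex or district would not reliably remove that.

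At stake is how the case-control results are read. The study is meant to inform a future trial of socioeconomic support, and preliminary Project 1 findings on social determinants feed the coding of the Project 2 data. A contrast on these three variables could be reported as smaller or larger than it is, with nothing in the planned check to warn of it.

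**Working it through.** There is no figure in the article to reproduce: the sample of about 200 cases and 100 controls is called pragmatic, with no rates, effect size or power. All prevalences and effect sizes below are assumptions, used only to show direction and possible size.

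**1. Mix of controls.** Five location types are listed and numbers per location are to be similar. Assuming equal numbers by type, 100 / 5 = 20 controls each: 20 from health centres, 20 from antenatal and immunization clinics, 20 from post-camp visits, 20 from tea houses, 20 from public places.

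**2. Comorbidity.** Assume 30% in cases and 15% in the population. Control prevalence is p = (sum of the five location prevalences) / 5, and OR = (0.30/0.70) / (p/(1 − p)).

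| Health centre | Post-camp | Antenatal / immunization | Other two | p | OR |
|---|---|---|---|---|---|
| 15% | 15% | 15% | 15% | 15.0% | 2.43 (no selection) |
| 22.5% | 22.5% | 15% | 15% | 18.0% | 1.95 |
| 30% | 30% | 15% | 15% | 21.0% | 1.61 |
| 15% | 15% | 7.5% | 15% | 13.5% | 2.75 |
| 15% | 15% | 5% | 15% | 13.0% | 2.87 |
| 22.5% | 15% | 7.5% | 15% | 15.0% | 2.43 (exact cancellation) |
| 22.5% | 22.5% | 7.5% | 15% | 16.5% | 2.17 |

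With 20% in cases and 10% in the population the pattern is the same. The OR without selection is (0.20/0.80)/(0.10/0.90) = 2.25. It falls to 1.54 if health-centre and post-camp controls are both at 20% (p = 14%), and rises to 2.53 if antenatal and immunization controls are at 5% and the rest at 10% (p = 9%).

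**3. TB knowledge.** Assume 70% of cases and 40% of the population know an item: OR = (0.70/0.30)/(0.40/0.60) = 3.50. If the 20 post-camp controls know as much as cases, p = 0.8 × 0.40 + 0.2 × 0.70 = 0.46 and OR = 2.74. If 40 of 100 controls do, p = 0.52 and OR = 2.15. If cases know less than the population, the same shift in controls widens the gap instead.

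**4. Quality of life.** Assume a case deficit of 0.50 SD. If a share s of controls has a deficit d, the contrast is 0.50 − s × d: from 0.50 − 0.2 × 0.25 = 0.45 SD to 0.50 − 0.4 × 0.50 = 0.30 SD. If instead a fifth of controls is 0.25 SD better than the population, it is 0.50 + 0.2 × 0.25 = 0.55 SD.

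**5. What the planned check can show.** None of the quantities varied in steps 2 to 4 is sociodemographic. Agreement with the national survey on education, occupation, amenities and assets is compatible with every row of the table.

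**The case against.** The strongest objection concerns direction. A reader might infer that recruiting at health services pulls all these contrasts towards no difference. The documents do not support that. The same list includes antenatal and immunization clinics, whose attenders need not be ill, and the working shows that this source alone moves the odds ratio away from 1 and can cancel a health-centre effect exactly. The article gives no reasons for attending the health centres and does not say that the camps include TB education. For knowledge, the sign also depends on whether cases, interviewed in months 3 and 6 of treatment, know more or less than the population. This objection stands, and the point is worded accordingly.

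Second, the matter is limited. The comparison is secondary, the study exploratory, and convenience sampling is openly acknowledged with its reasons. Of the three variables, only TB knowledge is named in the analysis section's list of compared variables, and comorbidities are not an item in the interview content under Study activities. This lowers the weight of the point. It does not remove it, because Secondary aims names all three.

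Third, recruiting some controls through the camps can give them a source population shared with the cases found by active case finding, which is a strength for that contrast. Restricting the main analysis to tea houses and public places would favour people well enough to be out, and could bias the other way. Both arguments stand, and they are why the main contrast should keep all controls.

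Finally, a reader might see a contradiction in the Ethical statement, which refers to "separate consent forms and information leaflets for patients and healthy controls". Eligibility is clearly defined elsewhere, so this is a matter of labelling. Nor does the point rest on the article's silence about stratification by location, which a fuller plan may cover. It rests on the recruitment routes and on the check that the article does specify.

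**Conclusion.** The concern holds as selection bias of uncertain net direction in the case-control contrasts for TB knowledge, comorbidities and quality of life. Attenuation is plausible from health-centre and post-camp controls, and the opposite is plausible from antenatal and immunization attenders. Under the assumed inputs, a comorbidity odds ratio of 2.43 could appear as anything from 1.61 to 2.87, including no change at all. These are illustrations that rest on assumed prevalences and equal numbers by location type, not estimates of the bias in this study.

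The planned comparison with the national survey cannot detect the problem, whichever way it runs. The effect is confined to a secondary aim and does not touch the cost analysis or the comparison of active with passive case finding among cases.

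**What to change.** - Keep all 100 controls as the main contrast.
- Confirm that recruitment location was recorded for each participant. The rule on similar numbers per location suggests it, but the article does not say so. If it was, carry it as an analysis variable.
- Report the TB-knowledge, comorbidity and quality-of-life contrasts by recruitment location.
- State these sensitivity analyses before analysis starts: for TB knowledge, leave out the post-camp controls; for comorbidities and quality of life, leave out the healthcare-recruited controls (health centres, antenatal and immunization clinics), then also the post-camp controls.
- Where these contrasts are reported, state this limitation specifically, with its direction as uncertain.

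The cost is precision in the restricted analyses. With 20 controls per location type they use 80, 60 and 40 controls. For a difference in means with equal SDs, interval width is proportional to √(1/200 + 1/n). Against n = 100 (0.1225), it is 8% wider at n = 80 (0.1323), 20% wider at n = 60 (0.1472) and 41% wider at n = 40 (0.1732). The main analysis loses nothing. Study status puts the start of analysis in February 2020, after nearly all data were collected, so the change affects analysis and reporting only, provided that location is on record.
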